Beta blockers, antiplatelet therapy, statins, angiotensin-converting enzyme inhibitors, and angiotensin receptor blockers will be allowed provided the dose has been stable for at least 4 weeks prior to the run-in period. If instances of an angina attack occur, nitroglycerine tablets can be used sublingually.During the intervention period, when combined medication is required for other diseases, the investigator should record the name of the medication, the reason for the medication, and the time of medication in detail.If infection, hyperglycaemia, hypertension, etc., are present in the intervention period, symptomatic drugs will be allowed provided the therapy does not affect the efficacy and safety of the test drug. All drugs used must be recorded for analysis and reporting in the summary.

The following medications are prohibited throughout the duration of the study treatment period. If banned drugs are used, those subjects will be withdrawn from the study.
Long-acting nitratesChinese medicinal preparations that are used for the treatment of coronary heart disease or may have the effects of promoting Qi, promoting blood circulation and removing blood stasisAnticoagulant drugsOther drugs that may affect the evaluation of test drugs

In this study, NXT, BYHW, the capsule placebo, and the granule placebo are provided by Shaanxi Buchang Pharmaceutical Co. Ltd. The capsule and granule placebos are similar to the study drug in smell, colour, specification, packaging, property of contents, and other features.

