#### Criteria for discontinuing or modifying allocated interventions {11b}

Participants are allowed to withdraw at any time without having to give a reason. The withdrawal criteria are as follows: (1) participants request withdrawal from the study; (2) there is exacerbation or deterioration that is clearly related to the treatment; (3) an allergic reaction that is clearly associated with the study drug occurs; (4) participants show comorbidities, complications, adverse events (AEs), or serious adverse events (SAEs) during the trial; (5) there is use of forbidden drugs or receipt of prohibited treatment; (6) participants show poor adherence, or the amount of drug used does not meet the regulations (< 80%); and (7) blinding is uncovered or emergency unblinding is required.

If a subject withdraws from the trial, no additional data will be collected, but the existing data will be used for statistical analysis. The time of treatment or trial discontinuation and the reason for withdrawal will be documented on the CRF. Drop-out patients will not be replaced.

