#### Strategies to improve adherence to interventions {11c}

Low adherence can have a substantial effect on statistical power and biased estimates of an intervention’s effect. To improve adherence to intervention protocols, during the treatment phase, we will distribute medicines once a week to evaluate the participant’s drug consumption and monitor adherence in a timely manner. Face-to-face adherence-reminder sessions will take place during the medicine dispensing process. After treatment, the drug package will be returned to the researchers. Compliance will be self-reported by participants and will be assessed by investigators at each visit. Compliance is calculated using the following formula: compliance = (actual amount of internal use/total amount of internal use) × 100%. Poor compliance is predefined as compliance < 80%. After 28 days of treatment, participants with poor compliance will be removed from the per protocol set (PPS).

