#### Provisions for post-trial care {30}

If SAEs occur during the study period, the participants are also required to be followed up after the study period. Appropriate measures will be taken to fully protect the interests of participants, such as outpatient or inpatient care or referrals to other specialists.

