### Procedure for unblinding if needed {17b}

Unblinding will be available if participants experience severe adverse events (SAEs) or need to be rescued in an emergency situation. Once unblinded, the participant will withdraw from the study. Researchers should report the reasons to the inspector within 24 h. The precise cause of unblinding, date of adverse events (AEs), treatment situation, and results must be recorded in electronic case record forms (eCRFs).

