### Methods in analysis to handle protocol non-adherence and any statistical methods to handle missing data {20c}

This study will be consistent with the CONSORT statement and intention-to-treat (ITT) principle, and the last observation carried forward method will be used for missing values. The full analysis set (FAS) is defined as all randomized patients who receive at least one dose of study medication. The per-protocol analysis set is defined as all eligible patients who are at least 80% compliant with the study drug and do not take the prohibited drugs during their time in the study. Analysis of the primary outcome and curative effect will be carried out using full-analysis-set and per-protocol-set approaches. The safety analysis set will include all randomized patients who have accomplished at least one study visit. Participating centres will be required to sum up the participant numbers in each centre and list participants who have been removed from the per-protocol set.

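### Withdrawal ends all data collection, so for patients withdrawn early the intention-to-treat analysis rests on carried-forward baseline scores instead of observed day-28 outcomes

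*Protocol article*

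**What the plan says.** All references are to the protocol article.

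- **After withdrawal {11b}:** "If a subject withdraws from the trial, no additional data will be collected, but the existing data will be used for statistical analysis". Patients who drop out are not replaced.
- **Withdrawal criteria {11b}:** seven are listed. Criterion (4) reads "participants show comorbidities, complications, adverse events (AEs), or serious adverse events (SAEs) during the trial", with no limit on grade or relatedness. Criterion (5) is use of forbidden drugs or treatment, criterion (6) is "participants show poor adherence, or the amount of drug used does not meet the regulations (< 80" percent), and criterion (7) is unblinding.
- **From the study, not only from treatment:** Intervention description {11a} says "If banned drugs are used, those subjects will be withdrawn from the study", and {17b} says "Once unblinded, the participant will withdraw from the study".
- **Analysis {20c}:** "This study will be consistent with the CONSORT statement and intention-to-treat (ITT) principle". Missing values are handled by LOCF. The full analysis set (FAS) is every randomized patient with at least one dose. The per-protocol set (PPS) requires eligibility, at least 80% compliance and no prohibited drugs.
- **Adherence elsewhere {11c}:** once the 28 days are over, "participants with poor compliance will be removed from the per protocol set (PPS").
- **Outcome timing (Primary outcome {12}, Tables 3 and 4):** the symptom score is taken at baseline and at day 28, with nothing in between.
- **Deterioration {11d}:** patients whose condition worsens so that they cannot continue are classed as treatment failures.
- **Safety follow-up {30}:** "If SAEs occur during the study period, the participants are also required to be followed up after the study period".

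**The concern.** An intention-to-treat analysis needs the outcome of each randomized patient whether or not treatment continued. Here, events after randomization that the treatment may itself cause (adverse events, poor adherence, a prohibited drug taken for uncontrolled symptoms) end outcome collection. The missing values are therefore produced by rule and are not plausibly unrelated to arm or response. With only two scheduled scores, LOCF has nothing but baseline to carry forward, so the analysed response rate mixes efficacy with the frequency of withdrawal. If withdrawal differs between NXT, BYHW and placebo, a difference in efficacy can be created, hidden or reversed.

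The sections also give different instructions for the same patient, so sites could legitimately differ on who has a day-28 score. A later analysis plan cannot repair this, because data that were never collected cannot be recovered.

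**Working it through.** **1. Reproducing the plan's sample size (Sample size {14}).** The inputs are rates of 85%, 70% and 50%, df = 2, alpha = 0.05 and power 0.80. Effect size: w² = Σaᵢ(pᵢ − p̄)² / [p̄(1 − p̄)], where aᵢ are the allocation weights.

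With equal weights, p̄ = 0.6833 and w² = 0.020556/0.216389 = 0.0950, so w = 0.30821. At N = 102 the noncentrality is 102 × 0.0950 = 9.689, power is 0.802 and beta is 0.198. Then 102/0.8 = 127.5, rounded up to 128, with 26 expected dropouts. All of this agrees with the article.

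**2. What LOCF does to a withdrawn patient.** The only score before day 28 is baseline, so the carried-forward change is zero and the patient counts as not improved. If a fraction d of an arm is withdrawn before day 28 and the planned rate p would apply to everyone, the analysed rate is p(1 − d).

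**3. Equal withdrawal in all arms.** This uses 2:1:1 weights and all 128 patients in the FAS.

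- d = 0: p̄ = 0.725, w² = 0.020625/0.199375 = 0.10345, noncentrality 128 × 0.10345 = 13.24, power **0.913**.
- d = 0.20: rates 68/56/40%, p̄ = 0.58, w² = 0.0132/0.2436 = 0.05419, noncentrality 6.94, power **0.651**.

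| Withdrawn per arm | Analysed rates NXT/BYHW/placebo (%) | Three-arm power |
|---|---|---|
| 0% | 85/70/50 | 0.913 |
| 10% | 76.5/63/45 | 0.791 |
| 20% | 68/56/40 | 0.651 |
| 30% | 59.5/49/35 | 0.518 |
| 40% | 51/42/30 | 0.403 |

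Inflating 102 to 128 allows for patients who are lost from the analysis. It does not allow for patients who stay in it as failures.

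**4. Unequal withdrawal, no true difference.** Take a true rate of 70% on both NXT (n = 64) and BYHW (n = 32), with withdrawal of 10% and 30%. The analysed rates are 0.70 × 0.90 = 0.63 and 0.70 × 0.70 = 0.49, pooled 0.5833.

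- SE under the null: √[0.5833 × 0.4167 × (1/64 + 1/32)] = 0.1067
- SE under the alternative: √[0.63 × 0.37/64 + 0.49 × 0.51/32] = 0.1070
- z = (0.14 − 1.96 × 0.1067)/0.1070 = −0.647, so the chance of a significant result favouring NXT is Φ(−0.647) = **0.26**, against a nominal 0.025.

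**5. Unequal withdrawal, true difference as planned.** With 85% against 70% and withdrawal of 30% on NXT and 10% on BYHW, the analysed rates are 0.85 × 0.70 = 59.5% and 0.70 × 0.90 = 63%. The direction reverses.

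**6. Sections side by side.**

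- *Adherence below 80%:* a withdrawal criterion in {11b}, so no later data; only a PPS exclusion in {11c} and {20c}, judged after day 28 in {11c}, so the day-28 score exists.
- *Adverse events and comorbidities:* a withdrawal criterion of any grade in {11b}. Yet {11a} permits symptomatic drugs for infection, hyperglycaemia or hypertension during treatment, and {22} has adverse events recorded at every visit with duration, result and follow-up time. Both presuppose that such patients continue.
- *Serious adverse events:* {11b} stops data collection, while {30} requires follow-up beyond the study period.

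**The case against.** A reader might infer that the intention-to-treat analysis cannot be done at all, or that every withdrawn patient lacks a primary outcome. The article does not support that. The FAS keeps all randomized and dosed patients in their arms, existing data are used, and LOCF supplies a value. Deterioration has its own rule in {11d}, which defines an outcome. A patient withdrawn late may still have been assessed, since Table 4 allows 28 ± 4 days. This objection stands, and it limits the point to imputed versus observed day-28 outcomes.

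A reader might also bound the NXT minus BYHW difference by letting the missing 20% be all successes in one arm and all failures in the other. That would run from 0.68 − 0.76 = −8 points to 0.88 − 0.56 = +32. It ignores the plan's own LOCF rule, under which equal 20% withdrawal gives 68% − 56% = 12 points against the planned 15. Nor is the 20% in {14} attributed to these criteria. It is a general allowance that may include withdrawn consent and loss to follow-up.

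The any-adverse-event reading of criterion (4) is the most literal one and may be loose wording in a condensed article. {11b} also asks for the time of treatment or trial discontinuation, so it names both events, and {30} keeps serious events under follow-up. These points soften the finding but do not answer it: no section provides for outcome assessment after study drug is stopped, and {11a} and {17b} say plainly that the patient leaves the study.

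**Conclusion.** The point holds in limited form. As written, {11b} creates missing day-28 outcomes through events that may depend on treatment, and LOCF then counts those patients as not improved. An analysis labelled intention-to-treat can be computed, but it would not rest on outcomes observed regardless of adherence or discontinuation.

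The figures in the working illustrate the size and do not forecast it. They assume that withdrawal comes before day 28, that LOCF of baseline means non-response, and that the planned rates would have applied to withdrawn patients. The 20% per arm and the 10%/30% splits are also assumptions, since the article gives no withdrawal rate by cause or arm. On that basis, three-arm power falls below the planned 0.80 already at 10% withdrawal per arm (0.791). Unequal withdrawal biases the NXT versus BYHW comparison in whichever direction withdrawal is unbalanced.

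Separately, the adherence and adverse-event rules contradict each other across sections and need reconciling however often withdrawal occurs.

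**What to change.** Separate stopping study drug from leaving the study. Replace the {11b} sentence on data after withdrawal with: *Participants who stop study medication for any reason remain in the study unless they withdraw consent to data collection; the day-28 symptom score, ECG, SAQ, nitroglycerine use and AEs are still collected and enter the FAS.*

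Keep the PPS exclusions as {20c} defines them. Turning every withdrawal criterion into a PPS exclusion would remove anyone with an adverse event or comorbidity, which {20c} does not do.

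The sponsor should reconcile {11a}, {11b}, {11c}, {11d}, {17b}, {22} and {30} on when treatment stops. That is a clinical decision, and no rule is proposed here.

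The cost is a protocol amendment in a trial that began in June 2018 and was still recruiting, plus effort to bring back patients who stopped drug. The day-28 visit is already in Table 4. Data from patients already withdrawn, or who refuse follow-up, will not be recovered.

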### Adverse event reporting and harms {22}

Both NXT and BYHW are Chinese medicines for promoting blood circulation and removing blood stasis. Their side effects may include mild gastrointestinal reactions such as stomach pain, nausea, and loss of appetite in a small number of patients. Very few patients may have symptoms such as skin itching, peeling, papules, drowsiness, upset, or headache, which can disappear after stopping the drug. As long as the medication is used correctly, the side effects will be appropriately reduced.

The investigator should explain and ask the participants to truthfully reflect changes in their condition after the medication, avoiding leading questions. While observing the curative effect, attention should be given to observing adverse reactions, AEs, or unexpected side effects (including symptoms, signs, laboratory tests). Regardless of whether the adverse reaction or AE is related to the trial drug, it should be recorded in detail, including the time of occurrence, symptoms, signs, severity, duration, laboratory test indicators, treatment methods and results, elapsed time, follow-up time, etc., and the combined medications should be described in detail for analysis of the correlation between the AEs and the trial drug.

During the treatment period, all AEs and SAEs should be monitored and recorded at every study visit. Once AEs occur, the researcher will evaluate whether they are related to the test drug and will judge the severity of the AEs. In cases of SAEs, the participating patients are asked to take immediate measures to protect their safety and report the events to the ethics committee within 24 h. The classification and coding of AEs are formulated according to the Common Terminology Criteria for AEs version 4.03.

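### The ban on collecting data after withdrawal has no safety exception and conflicts with the protocol's own rules for recording how adverse events end

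*Protocol article*

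**What the plan says.** Section {11b} (criteria for discontinuing or modifying interventions) numbers seven withdrawal criteria. The fourth is that "participants show comorbidities, complications, adverse events (AEs), or serious adverse events (SAEs) during the trial". The second and third require a clear link to treatment or study drug; the fourth sets no threshold of severity or relatedness. The section then gives the rule for everyone who leaves: "If a subject withdraws from the trial, no additional data will be collected, but the existing data will be used for statistical analysis". Only the time of discontinuation and the reason are to be documented.

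Three other sections ask for more:

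- Section {22} (adverse event reporting and harms) requires each AE, related or not, to be recorded in detail, including "severity, duration, laboratory test indicators, treatment methods and results, elapsed time, follow-up time".
- Section {17b} (unblinding) says "Once unblinded, the participant will withdraw from the study", and ends with this duty: "The precise cause of unblinding, date of adverse events (AEs), treatment situation, and results must be recorded in electronic case record forms (eCRFs").
- Section {30} (post-trial care) says "If SAEs occur during the study period, the participants are also required to be followed up after the study period".

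On analysis, section {20c} says "The safety analysis set will include all randomized patients who have accomplished at least one study visit", so patients who withdraw after a visit remain in the safety set. The same section says that "the last observation carried forward method will be used for missing values".

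**The concern.** Safety is a stated aim of the trial alongside efficacy. For a patient who leaves because of an adverse event, the key facts are whether it resolved, how long it lasted and what treatment it needed. If the event is still open at exit, those facts do not yet exist and can only come from contact after withdrawal. Section {11b} rules that contact out as a source of trial data, while section {22} demands what it would yield.

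The same rule cuts short the search for new events. Completers are observed for the full four weeks; a leaver is observed only to the day of exit. A later AE, or a worsening to serious before day 28, would go unrecorded.

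This is a conflict between stated rules, so the brevity of a journal article does not explain it. A later analysis plan cannot repair it either, because it cannot restore data that sites did not collect.

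**Working it through.** The plan gives no figure for this point, so the check compares the rules case by case and then sets an upper bound on the number of patients.

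**Which rule applies to a patient who leaves early?**

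1. *Event resolved before exit.* Its duration, treatment and result already exist, section {11b} keeps existing data, and section {22} is satisfied. No conflict.
2. *AE unresolved at exit, no unblinding.* Section {22} wants duration, results and follow-up time. Section {11b} forbids further collection. Neither refers to the other or says which prevails. Direct conflict.
3. *SAE with emergency unblinding.* Section {17b} withdraws the patient and requires the results to be recorded. Unblinding is also the seventh withdrawal criterion in {11b}, so the ban applies on its face. As the more specific rule, {17b} may be taken to govern, but the text does not say so.
4. *SAE without unblinding.* Section {30} requires follow-up, but under a heading about care and without saying that the findings enter the trial record. Section {22} still asks for the outcome and {11b} still bars it. Conflict.
5. *New AE or SAE after exit and before day 28, whatever the reason for leaving.* Section {22} ties recording to study visits in the treatment period, and a withdrawn patient has none. Section {11b} closes the other route. The event is missed.

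**How many patients could this touch?**

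The inputs come from the sample size section {14}: 102 evaluable patients and 20% dropout.

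- Inflated total: 102 / (1 − 0.20) = 127.5, rounded up to 128, which reproduces the plan's figure.
- Expected dropouts: 128 − 102 = 26, again as stated.
- Share of those randomized: 26 / 128 = 20.3%.

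The 26 cover every reason for leaving. Patients with an event open at exit (cases 2 to 4) and patients with a new event before day 28 (case 5) are subsets of them. The documents give no AE rate and no breakdown of dropout by reason, so 26 is a ceiling and not an estimate. It holds only if dropout does not exceed the planned 20%.

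**What is not lost?**

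The event that led to withdrawal is recorded under {22}. Data up to exit are kept under {11b}. A patient withdrawn for an AE already counts in the between-arm comparison of AE proportions in section {20a}.

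**The case against.** The best defence is that the rules can be read together: {11b} stops scheduled trial assessments, and the harms section, which covers every AE and is not limited to patients still on study, governs event follow-up. Sections {17b} and {30} point the same way. This is probably what was intended. But {11b} says that no additional data will be collected, without qualification, and nothing ranks the harms section above it. A site reading {11b} alone would stop.

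A second defence is that the Discussion concedes, as a limitation, that AE recording is confined to the four treatment weeks. That stands, and it is why day 28 is a sensible limit for new events. It does not cover a patient who leaves earlier within those weeks.

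Two stronger readings are tempting, and the documents support neither.

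- A reader might infer that any AE automatically removes a patient. Section {11a} allows symptomatic drugs for infection, hyperglycaemia or hypertension arising during treatment, and section {22} expects events to be recorded at every visit, so some patients with events evidently continue. The fourth criterion is better read as a loosely worded ground for withdrawal.
- A reader might infer that last observation carried forward will put pre-treatment laboratory values into the day-28 safety comparison, since laboratory tests are scheduled only at baseline and day 28. Section {20c} names no outcome class, but it states the method in the same sentence as the intention-to-treat principle, just before the full analysis set, and never mentions laboratory data. An analysis plan could limit it to efficacy. Any figure for the resulting distortion would rest on invented dropout patterns.

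**Conclusion.** The point holds as a conflict between stated rules on safety data. For a patient withdrawn with an unresolved event, a site that follows {11b} loses the outcome that {22}, and after unblinding {17b}, require; it also misses any new AE or SAE before day 28. The conflict is plainest for AEs and SAEs without unblinding, where no more specific withdrawal rule is available.

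The size is unknown, with 26 of 128 patients as the ceiling under the planned dropout. The real number depends on how often sites use the fourth criterion and on how many events are open at exit; the documents give neither. Nothing here challenges the primary efficacy comparison or the recording of the event that caused withdrawal. The correction is worth making because it is cheap and because uncollected outcomes may not be recoverable later.

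**What to change.** Amend section {11b} so that the ban on further data does not extend to safety. For example: after withdrawal, unless the patient refuses, the duration, treatment, result and follow-up time of any AE or SAE, and any new AE or SAE up to day 28, will still be collected and entered in the trial record. A cross-reference to {22}, {17b} and {30} would remove the remaining doubt.

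The cost is a short amendment and a notice to six sites while recruitment is in progress, plus some contact with patients who have left. Some will decline, and patients already withdrawn may not be recoverable.

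As an optional clarification, {20c} could state that last observation carried forward applies to efficacy outcomes and that laboratory and vital-sign data are analysed as observed. The main correction does not depend on it.
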